### Specific Aims and Hypotheses

Overall, the study aims to examine the neural correlates of early weight gain in adolescents with AN undergoing FBT with MRI scans conducted at baseline prior to initiating treatment, after session 4 (the point at which weight gain is predictive of clinical EOT response), and again at EOT (18 sessions of treatment, approximately 6 months with a maximum of 9 months). Although this study is designed to provide evidence of feasibility in conducting neuroimaging in the context of FBT and establish preliminary effect sizes to guide future research, we provide the following specific hypotheses that we hope to explore in this pilot study. We hypothesize greater increases in brain volumes, surface area, and cortical thickness from pre-treatment to session 4 in those who gain more than 2.4 kg during that time. We also hypothesize that network connectivity and activity during r-fMRI will show greater changes in adolescents with early weight gain compared to those who do not show early weight gain. Specifically, we predict greater increases in default mode activity and reductions in SN activity from pre-treatment to session 4 in those who gain more than 2.4 kg during that time (47). We also hypothesize improvements in white matter integrity, measured with DTI, in those who gain more than 2.4 kg by session 4 compared to those who do not, providing evidence that consistent nutritional improvements can have rapid impact on brain connectivity (48). We also hypothesize improvements in functional tasks related to cognitive and emotional functioning in those who gain more than 2.4 kg by session 4. Specifically, we expect improvements in a task-switching task as evidenced by improved behavioral performance and altered brain activity in prefrontal cortex and superior parietal cortex. During a food image task, we expect to find reduced amygdala activity in response to food versus non-food images over time in those who show early weight gain. Although the primary aim relates to neural changes at session 4 (the time where early weight gain is predictive of outcome), a secondary aim is to examine these measures at EOT, which will allow us to capture any neural changes that may be more delayed, requiring longer length of time or more weight gain for recovery. This secondary aim is in place due to the preliminary nature of the protocol, since there is no prior research related to early treatment effects. In other words, this aim increases the likelihood to detect effects given that prior research on weight restoration in AN has shown improvements across these domains.

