
## Methods

### Participants

Participants for this study will be recruited directly from an existing RCT. The RCT is testing an adaptation to standard FBT wherein adolescents who do not gain 2.4 kg by session 4 are randomly assigned to either continue standard FBT or to receive Intensive Parent Coaching (IPC) which involves an additional intense scene during session 4 to increase urgency to act in the parents, a parent-only session to further support parental behavior change for refeeding, and an additional family meal for greater support and guidance of parent refeeding behaviors. Prior research informed the selection of 2.4 kg as the marker of early treatment response. Five studies identified early weight gain in FBT as a possible marker of early treatment response (2–4, 6, 49) converging on a consistent weight gain range of 2–3 kg by session 4. Unpublished data on early response from the largest multi-site study of FBT for adolescent AN (2) matched the weighted average of the current published studies, a weight gain of 2.4 kg by session 4. An additional study by Hughes and colleagues (50) found that 2.8 kg by session 5 was the most sensitive predictor of remission. However, this study involved twice weekly sessions for the first 2 weeks with session 5 occurring on week 3 of treatment (unlike 1 session per week in other trials). This increased intensity of treatment delivery may have shifted the timing and amount of early weight gain predictive of remission by end of treatment (50). Thus, the proposal settled on 2.4 kg by session 4 as the marker of early response. Importantly, we considered the use of change in percentage ideal body weight or BMI-SDS (body mass index standard deviation score) per age, but the prior research showed these predictive effects with the actual weight gained regardless of initial weight, height, age, or sex.

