Because participants will be recruited for the neuroimaging study prior to the start of treatment, we cannot balance the numbers of participants in a particular treatment arm. All study participants who meet eligibility criteria and are able to visit Stanford University for three imaging appointments will be invited to participate. Although the main RCT is being conducted at two sites (Stanford University and University of California, San Francisco), they are both located in the San Francisco Bay Area, and thus, are both potential sites for the recruitment of participants for this neuroimaging component. The population of the Bay Area is large and diverse, and the RCT makes specific efforts to recruit minorities for the study. The target sample size for this preliminary study is 20 in order to establish feasibility of including neuroimaging to an RCT of FBT and obtain preliminary effect sizes. Inclusion criteria include: 12–18 years of age that meet DSM-5 criteria for AN and participating in the RCT testing IPC for early non-response to FBT. Exclusion criteria include: 1) associated physical illness that necessitates hospitalization; 2) psychotic illness or other mental illness requiring hospitalization; 3) current dependence on drugs or alcohol; 4) physical conditions (e.g., diabetes mellitus, pregnancy) known to influence eating or weight; 5) Wechsler Abbreviated Scale of Intelligence (WASI) scores below the low average range defined by the test (<80); 6) family history or current child abuse or neglect (when reported in response to a question on phone screen, the perpetrator of abuse is excluded from family treatment, but the adolescent may participate with the rest of the family); 7) previous FBT for AN; 8) contraindications for MRI (e.g., orthodontia, metallic implants); 9) current or past major neurological (e.g., seizure disorder, psychosis, head trauma) or major sensory deficit. Participants are withdrawn from the study if any of the following occur: 1) sexual or physical abuse by a family member; 2) hospitalization for >21 days; 3) missing >4 consecutive appointments; worsening of psychiatric conditions such that participant would be clinically better served by referral for other treatment; 4) participant undertaking other psychotherapies during the treatment study. Visual acuity is determined by self-report, and participants with corrected vision use MR-safe lenses during scans.

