DTI data will be analyzed with FSL Diffusion Toolbox (FDT) to perform affine registration to correct for eddy current distortions, extract brain from skull in the image, and fit tensors and tracts to the data. Further tensor fitting and fiber tracing will be completed with Diffusion Toolkit software. Primary measures will be of fractional anisotropy (the degree to which diffusion takes place in a given direction) and R1 (measure of relaxation rates of water protons, which has a strong relation with myelin content). Probabilistic tractography will be explored using FSL’s built-in tools, particularly along fronto-striatal pathways, which may be impacted in AN (74). Of note, DTI data, as well as structural data, can be impacted by effects of dehydration, which may relate to malnutrition (75). Although objectively assessing hydration status specifically would be ideal, it is not possible in this small study. However, we will include reports of hydration, as well as recent hospitalizations, as many of the patients in the trial were in the hospital for medical stabilization (including hydration) prior to enrolling in the study.

Behavioral data from the risk-taking task will be examined by calculating the adjusted score, which is the average number of casts taken on rounds when participants chose to stop fishing. Higher scores indicate greater risk-taking.

Across all measures (gray and white matter volume, cortical surface area, cortical thickness, r-fMRI connectivity for SN and DMN, DTI FA and R1, task-based contrasts, and risk-taking scores), we will examine change over time using repeated measures analyses, including mixed effects modeling for extracted scores or repeated measures modeling in FSL for task-based measures. Because EOT will occur at different times after baseline depending on treatment duration, time will be included as a covariate. Primary comparisons will be conducted between those who gain 2.4 kg by session 4 and those who do not (early responders vs. non-early responders). We will also use weight change as a continuous variable to examine how change in the brain and behavior measures is associated with weight change, particularly if we have small cell size in one of the two responder groups. Exploratory analyses will also examine baseline brain and behavior measures as predictors of early response and end of treatment outcome *via* mixed effects.

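### At end of treatment the non-early-responder group mixes standard FBT with IPC, so the secondary EOT responder contrast cannot be read as early response under FBT

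*Protocol article*

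**What the plan says.** Under Methods, Participants, the article says of the imaging sample: "Participants for this study will be recruited directly from an existing RCT". In that RCT, "adolescents who do not gain 2.4 kg by session 4 are randomly assigned to either continue standard FBT or to receive Intensive Parent Coaching (IPC". Nothing in the article randomises early responders or offers them IPC. The same section concedes that, because recruitment precedes treatment, "we cannot balance the numbers of participants in a particular treatment arm". On size it says: "The target sample size for this preliminary study is 20 in order to establish feasibility"; the other stated purpose is preliminary effect sizes.

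Specific Aims and Hypotheses places the primary aim at session 4 and adds that "a secondary aim is to examine these measures at EOT", in order to catch neural change that takes longer or needs more weight gain.

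The comparison is set in the closing paragraph of the Data Analytic Plan (under Functional Data Preprocessing). It covers all the imaging and behavioural measures with repeated-measures or mixed models, and says: "Primary comparisons will be conducted between those who gain 2.4 kg by session 4 and those who do not". On EOT it adds: "Because EOT will occur at different times after baseline depending on treatment duration, time will be included as a covariate". A further analysis uses weight change as a continuous variable. For diffusion and structural data, reports of hydration and of recent hospitalisation are also to be included. Treatment arm appears nowhere in the analysis.

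**The concern.** Up to session 4 the two responder groups are on the same treatment. After it, the non-early responders divide into FBT and IPC while the early responders do not. A two-group comparison at EOT therefore differs in two respects at once: early response, and exposure to a second treatment given to part of one group only.

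IPC is meant to strengthen parental refeeding, and the study expects weight gain to be accompanied by neural change. If both hold, IPC narrows the EOT gap by an amount that depends on how many imaging participants happened to be allocated to it. A null EOT result could then reflect either no delayed difference or catch-up on IPC, and the analysis as described could not tell these apart. An effect size carried into a later study would not describe early response under FBT.

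**Working it through.** The article gives no power calculation or effect size to reproduce, so the check is structural, followed by an illustration.

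**Inputs from the article.** Only non-early responders are randomised (Participants). The total target is 20 (Participants). The groups are early responders and all non-early responders (Data Analytic Plan). EOT is a secondary time point (Specific Aims and Hypotheses).

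**Assumptions, not in the article.** 10 of the 20 are non-early responders; allocation is 1:1; the within-group SD is 1; no one is lost before EOT; the true EOT gap between early responders and FBT-only non-responders is 0.8 SD; IPC closes 25%, 50% or 75% of it.

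**Structure.** Score each measure so that higher is better. Let π be the IPC share among non-early responders and δ the IPC effect on the measure. The mean of the pooled non-early responders is the FBT-only mean plus πδ, so

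pooled contrast = (early responders − FBT-only non-responders) − πδ.

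The second term vanishes only if π = 0 or δ = 0. If IPC worsened a measure, its sign would reverse.

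**Size at a gap of 0.8 SD.**

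| Fraction closed | δ (SD) | IPC count of 10 | πδ | Pooled contrast |
|---|---|---|---|---|
| 25% | 0.2 | 5 | 0.10 | 0.70 |
| 50% | 0.4 | 2 | 0.08 | 0.72 |
| 50% | 0.4 | 5 | 0.20 | 0.60 |
| 50% | 0.4 | 8 | 0.32 | 0.48 |
| 75% | 0.6 | 5 | 0.30 | 0.50 |

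**Chance in the split.** With 10 non-responders and 1:1 allocation, the central 95% binomial range of the IPC count is 2 to 8. A 7:3 or more uneven split has probability 352/1024 = 0.34. With 6 or 14 non-responders the corresponding range of π is 0.17 to 0.83 or 0.21 to 0.79.

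**Price of separating the arms.** With 10 early responders, the variance of the pooled contrast is 1/10 + 1/10 = 0.20. For the FBT-only contrast at 5:5 it is 1/10 + 1/5 = 0.30, so the interval is √(0.30/0.20) = 1.22 times as wide. Mean squared error (MSE) for the FBT-only target, taken as bias² + variance:

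| Fraction closed | IPC count of 10 | Pooled | FBT-only |
|---|---|---|---|
| 50% | 5 | 0.20² + 0.20 = 0.24 | 0.30 |
| 50% | 2 | 0.08² + 0.20 = 0.21 | 1/10 + 1/8 = 0.23 |
| 50% | 8 | 0.32² + 0.20 = 0.30 | 1/10 + 1/2 = 0.60 |
| 75% | 5 | 0.30² + 0.20 = 0.29 | 0.30 |

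The FBT-only contrast removes the bias but is too imprecise at this size to win on mean squared error in any of these cases.

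**The case against.** The strongest reply has five parts.

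- **The plan's primary comparison is at session 4, and EOT is secondary.** This stands. A reader might infer that the primary contrast is contaminated too, since the first IPC component is delivered in session 4 and the scan follows it. The article gives no ground for thinking that a single parent-directed scene alters brain measures before that scan, so this remains speculation.
- **The article never spells out a responder contrast at EOT.** It is an inference, but a fair one: the grouping is stated for all measures over time, in the same paragraph that deals with the varying date of EOT.
- **Covariates are commonly left to an analysis plan that is not shown.** This stands in part. The article's list is not exhaustive, and a reader who took time to be the only covariate would overlook the hydration and hospitalisation reports. But the article does fix the groups and an adjustment for EOT, and leaves out the randomised treatment it describes itself. None of the adjustments it names separates the arms.
- **The continuous weight-change analysis covers the problem.** It does not. It relates brain change to weight change and so answers a different question. IPC aims to change later weight, so that analysis does not recover the early-response contrast.
- **The pooled contrast is a legitimate estimand, and more precise.** This stands. It describes early response under the RCT's mix of treatments, and the mean squared errors above favour it.

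**Conclusion.** The point holds for the secondary EOT comparison, at moderate severity. As described, that comparison estimates the FBT-only contrast less πδ. It cannot be read as the effect of early response under FBT, and a null result could reflect catch-up on IPC. The algebra needs only the article's own design. The sizes (0.48 to 0.72 SD in place of 0.8 when IPC closes half the gap) rest on an assumed gap, IPC effect, allocation ratio and number of non-responders. With no IPC effect on a measure the shift is zero.

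Two stronger conclusions that a reader might draw are not supported. One is that the pooled contrast should be replaced: the precision figures argue against that in a sample of 20. The other is that the exploratory models predicting EOT outcome from baseline measures must carry an IPC term: arm is assigned after baseline and at random among non-responders, so it does not confound those baseline predictors, and the term is optional. The feasibility purpose limits the consequence without removing it, because the effect sizes are meant to guide later research.

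**What to change.** For EOT data, add an IPC-by-EOT term that is zero at baseline and session 4, or use a three-level group: early responder, non-responder on standard FBT, non-responder on IPC. Report early responders versus FBT-only non-responders alongside the pooled contrast, and give the number in each arm at each scan. Label the pooled contrast as describing early response under the RCT's mixed treatment policy. State this before EOT data are examined.

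No session-4 scans need to be dropped. The RCT already records arm, so the cost is analysis wording and one extra model term. The downside is small cells (about 5 per arm under the assumptions above) and an FBT-only interval roughly 22% wider at a 5:5 split, and wider still if few non-responders stay on FBT. For that reason the added contrast should accompany the pooled estimate and not displace it.

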## Discussion

Studies of neural change over the course of treatment in anorexia nervosa, particularly early in treatment, have the potential to increase motivation for early refeeding behavior among parents of adolescents. A recently developed treatment incorporating neurobiological research findings into treatment was considered helpful in improving understanding of AN (76), suggesting that improving knowledge about neurobiological changes through treatment may be of interest to patients and families. Anecdotally, we often hear parents and clinicians express concern about not directly targeting eating disorder cognitions early in treatment. There is worry that focusing on refeeding ignores the emotional needs of the patient. Evidence of neural change early in FBT could alleviate these concerns by showing how cognitive and neurobiological functions can be impacted without being specific targets of treatment. Further, while brain plasticity during adolescence may create a vulnerability under which AN develops (77), it can also allow for greater opportunities for neural changes (78), providing some explanation why AN that is not treated during adolescence may become enduring (79).

Conducting neuroimaging research in the context of treatment for adolescent AN comes with a number of challenges. First, families are often anxious when first receiving a diagnosis and report feeling overwhelmed by deciding on treatment. It can be difficult for families to agree to participate in a study that does not have an immediate, tangible benefit for their child’s care. Later in recovery, we find that families may be more open to neuroimaging research, but at that point, we can no longer obtain pre-treatment data. Second, the timing of scans can create challenges in obtaining complete data for all participants. Families often, understandably, want to begin treatment as soon as possible, so scheduling a pre-treatment scan can feel like a delay of treatment. Our team often conducts scans on the same day as and just prior to session 1 in order to assuage this concern. Follow-up scans are also challenging to schedule, particularly the early treatment timepoint because there is a short window of time to complete the scan. Illnesses, busy schedules for scanners, or technical problems with the scanner can impact the collection of these data. Our team addresses this by scheduling the early response scan as early as possible so that it is on everyone’s schedule in advance, and our research coordinators are in constant communication with families to ensure that the timeline will still work. Scheduling as early in the time window as possible also allows for some buffer to reschedule in case of illness or technical problem. Finally, there may be a bias in samples for neuroimaging studies due to mistrust of research (80), anxiety about adding too much to the child’s schedule, or other reasons for declining participation (81). Although some of these biases may be exacerbated in neuroimaging studies of treatment effects due to the additional burden of assessment and treatment sessions being scheduled simultaneously, they may also be true of neuroimaging studies broadly. Thus, generalization of results must be made cautiously.

Overall, investigating brain and behavior changes over the course of FBT has great potential to improve our understanding of early treatment response and motivate engagement in treatment from the start. While many of the most pronounced neural differences in AN seem to recover with weight restoration, knowledge about how early these changes occur can support timing of treatment interventions. Further, a greater understanding that specific interventions targeting cognitive processes may not be necessary for neural and cognitive change can address fears that some families express about engaging in FBT. If hypotheses are supported from this preliminary study and in later confirmatory studies, future research could examine the influence of education about neurobiological change on treatment engagement. Further, if baseline brain function is predictive of treatment response, future research could consider augmentations or alternative treatments for those patients at high-risk for non-response.

## Data Availability Statement

The dataset for this study will be available upon study completion.

## Ethics Statement

This protocol was approved by the IRB at Stanford University. Written informed consent will be obtained from all participants.

